##### Interim analysis for futility

The success rate will be determined after 16 patients have been accrued and completed treatment. If fewer than nine successes are observed, consideration will be given to re-examining the cause of the lack of success and the trial could be re-designed or stopped for futility at this point. However, recruitment will continue while this futility boundary is evaluated. If nine or more success are observed, 30 additional patients will be accrued for a total of 46 patients. The main analysis will be performed after at least 46 patients have been followed for 2 years, or the data is sufficiently mature to report the results earlier.

Exploratory analyses comparing outcomes of the KIM ‘failures’ to KIM ‘successes’ will also be performed to obtain estimates of whether the degree of accuracy afforded by KIM actually translates to clinical endpoints.

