##### Acute / late toxicity and disease outcome assessment

Patients will undergo clinical assessment as well as routine blood tests, imaging at pre-defined time points as outlined in Fig. 2. Both acute and late toxicity will be reported using NCI Common Terminology Criteria for Adverse Events (CTCAE) version 4 and Radiation Induced Liver Disease (RILD).

Treatment response will be assessed by triple-phase CT or MRIs for patients with HCC. For patients with metastatic liver disease, local control will be assessed with CT scan and /or PET CT or MRI. The preferred assessment for HCC is the modified RECIST criteria [22] and for metastatic disease RECIST and/or PERCIST criteria [23].

Patient-reported outcomes (PROs) will be assessed using the general EORTC QLQ-C30 and disease specific quality of life questionnaires EORTC QLQ-HCC18.

In this study, 46 patients are needed to test the hypothesis that KIM can improve patient dose distribution.

We consider a treatment a success if the KIM-corrected patient dose distribution improves the planning target volume (PTV) dose to 95% of the volume (D_95_) or the liver dose to 50% of the volume (D_50_) by 5% compared to dosimetry without KIM. A dose accumulation method [24] will be used to determine the efficacy of KIM, where the isodose distributions and dose volume histograms for each treatment course will be calculated with KIM corrections as treated, and estimated without KIM corrections.

A 60% or higher treatment success rate would suggest KIM is promising and worthy of further investigation. Alternatively, a treatment success rate of 40% or lower would suggest than KIM should not be considered for this treatment modality. Using Simon’s two-stage optimum design [25], a sample size of 46 patients will have 80% power with 95% confidence to rule out a 40% success rate in favour of a more interesting success rate of 60%.

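### The stated 80% power and 95% confidence belong to a Simon design that stops at 7 or fewer of 16, not to the advisory rule printed at fewer than nine

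*Protocol article*

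**What the plan says.** The sample-size paragraph, at the end of the Protocol article's section on acute / late toxicity and disease outcome assessment, names the design and its error rates: "Using Simon’s two-stage optimum design [25], a sample size of 46 patients will have 80% power with 95% confidence". The uninteresting rate is 40% ("a treatment success rate of 40% or lower would suggest than KIM should not be considered for this treatment modality") and the interesting rate is 60% ("A 60% or higher treatment success rate would suggest KIM is promising and worthy of further investigation").

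The section on the interim analysis for futility then sets the look: "The success rate will be determined after 16 patients have been accrued and completed treatment". The boundary and its consequence are: "If fewer than nine successes are observed, consideration will be given to re-examining the cause of the lack of success". It goes on to say that "the trial could be re-designed or stopped for futility at this point. However, recruitment will continue while this futility boundary is evaluated". With nine or more successes, 30 further patients are accrued, for 46 in total. The article does not oblige the trial to stop below the boundary, and it prints no number of successes needed among the 46.

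**The concern.** Alpha and power in a Simon design are properties of one complete rule: a stage-1 boundary at which the trial stops without rejecting, and a final cut-off for trials that pass it. Some trials with a poor first stage would recover and reach the final cut-off by chance. Stopping removes them, and the final cut-off is set on that basis.

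The article departs from this rule in two ways. It makes the stop optional, which can raise the false-positive rate. It also prints a boundary one success higher than the optimum design uses, which lowers power if the boundary is obeyed. This is the only decision rule for the primary hypothesis in a single-arm trial, so the quoted error rates should describe the procedure that will be followed. The advisory clause would often apply: at a true success rate of 40%, the chance of fewer than nine successes in 16 is 0.858.

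**Working it through.** **Inputs.** From the sample-size paragraph: p0 = 0.40, p1 = 0.60, power 0.80, and 95% confidence, read as one-sided alpha 0.05 as is usual for Simon's design. From the interim section: n1 = 16, printed futility boundary 8 or fewer, 30 more patients, N = 46.

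**Formulas.** Let r1 be the largest stage-1 count that stops the trial and c the number of successes needed at the end.
- Boundary enforced: P(reject | p) = Σ over x from r1+1 to 16 of Bin(x; 16, p) × P(Y ≥ c − x), with Y ~ Bin(30, p).
- Boundary ignored: P(reject | p) = P(X ≥ c), with X ~ Bin(46, p).

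**Step 1: reproduce the plan's figure.** An exact search over total sizes 30 to 55, requiring alpha ≤ 0.05 and power ≥ 0.80 and minimising expected size at 40%, returns n1 = 16, r1 = 7, N = 46, c = 24. Alpha is 0.0486 and power 0.8006. The chance of stopping at 40% is 0.7161, so the expected size is 16 + (1 − 0.7161) × 30 = 24.5. The 16 + 30 = 46 therefore reproduces, with a stop at 7 or fewer. With r1 = 7, only c = 24 meets both targets: c = 23 gives alpha 0.077 and c = 25 gives power 0.755.

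**Step 2: vary the boundary and whether it binds.**

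| Stage-1 rule | Final cut-off | Alpha | Power |
|---|---|---|---|
| Stop at ≤7/16, enforced | ≥24/46 | 0.0486 | 0.801 |
| Stop at ≤8/16 (printed), enforced | ≥24/46 | 0.0348 | 0.684 |
| Boundary always overridden | ≥24/46 | 0.0636 | 0.891 |
| Boundary always overridden | ≥25/46 | 0.0343 | 0.825 |
| Stop at ≤7/16, enforced | ≥25/46 | 0.0281 | 0.755 |
| Stop at ≤8/16 (printed), enforced | ≥25/46 | 0.0213 | 0.653 |

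At a true rate of 60%, the printed boundary would stop the trial with probability 0.284, against 0.142 for a stop at 7 or fewer. That is where the power goes.

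**Step 3: partial override.** Suppose a below-boundary trial continues unchanged with probability q, whatever the count observed, and is judged at ≥24/46. Each error rate then moves linearly between its enforced and ignored values.
- Stop at ≤7: alpha passes 0.05 at q = (0.05 − 0.04859) / (0.06357 − 0.04859) ≈ 0.09.
- Stop at ≤8 (printed): alpha passes 0.05 at q = (0.05 − 0.03484) / (0.06357 − 0.03484) ≈ 0.53.
- Stop at ≤8 (printed): power reaches 0.80 only at q = (0.80 − 0.68375) / (0.89067 − 0.68375) ≈ 0.56.

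Under the printed boundary, no constant q meets both targets. A specific pattern, such as always continuing at exactly 8 of 16 and always stopping below that, would restore Simon's figures, but the article states none.

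**The case against.** A non-binding futility rule is a recognised choice, and 46 patients can support one. With ≥25/46, alpha is at most 0.034 and power is 0.825 if all 46 are treated, so both stated targets can be met. The article gives no final cut-off, which an article may leave to the full protocol or the analysis plan, so its absence is not a fault here. The excess in alpha is at most 0.0636 − 0.05, about 1.4 percentage points, in a phase II trial where a positive result leads only to further investigation. All of this stands. It limits the size of the problem, but it does not make the quoted figures properties of the printed rule.

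A reader might go further in three ways that the documents do not support.
- **That the 95% confidence is definitely not met.** The cut-off of 24 is inferred from the named design. The 6.4% also needs every below-boundary trial to continue unchanged, a path that the article leaves open but does not describe. Under the printed boundary, alpha stays within 5% unless overrides are more likely than not (about 53%).
- **That recruiting during the look inflates alpha.** It does not, provided the decision on the first 16 is then enforced for the test.
- **That the first 16 patients will be pooled with those treated after a redesign.** The article does not say so. It leaves their status open, and a redesigned trial has no defined error rate until that is settled.

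**Conclusion.** The point holds as a mismatch between the claimed error rates and the procedure described. With the final cut-off that belongs to the named design (≥24/46), the advisory wording allows alpha up to 0.064 against 0.05, and enforcing the printed boundary gives power of 0.684 against 0.80. The power shortfall, about 12 percentage points, is the larger of the two. Neither claim is shown to fail in every reading; what can be said is that neither is guaranteed.

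The conclusion rests on three assumptions: one-sided alpha of 0.05, exact binomial probabilities at 40% and 60%, and the inferred cut-off of 24. The figure of 0.064 is the worst case for continuing unchanged.

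**What to change.** Before the interim data are seen, choose one of these and write it in.

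(a) **Binding.** Bring the printed boundary into line with Simon's design and make it binding for the test: with 7 or fewer successes in 16, the 40% rate is not ruled out whatever follows, and success needs 24 or more of 46. Alpha is 0.049 and power 0.80.

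(b) **Advisory.** Keep the look advisory and set the final cut-off at 25 or more of 46. Restate alpha as at most 0.034 and power as 0.825 if the trial runs to 46. Add that power is 0.755 if it stops at 7 or fewer of 16, and 0.653 if it stops at the printed 8 or fewer.

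Under either option, state that if the trial is redesigned after the look, patients treated before the redesign do not count in the redesigned test. Recruitment may continue during the look.

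The cost is one or two sentences and no added patients in the planned 46. Option (b) asks for one more success at the end. Setting the rule after the interim result is known would make any choice look data-driven.

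### The interim cut-off of nine successes in 16 is one higher than in the Simon optimum design that the stated 80% power belongs to; if enforced as a stopping rule, it lowers power to about 68%

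*Protocol article*

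**What the plan says.** The sample-size paragraphs of the protocol article (at the end of the section Acute / late toxicity and disease outcome assessment) set the two benchmark rates: "A 60% or higher treatment success rate would suggest KIM is promising and worthy of further investigation", and "a treatment success rate of 40% or lower would suggest than KIM should not be considered for this treatment modality". They then name the design, "Using Simon’s two-stage optimum design [25], a sample size of 46 patients", and claim that "a sample size of 46 patients will have 80% power with 95% confidence to rule out a 40% success rate" in favour of 60%.

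The section Interim analysis for futility gives the stage-1 look: "The success rate will be determined after 16 patients have been accrued and completed treatment". The lower branch reads "If fewer than nine successes are observed, consideration will be given to re-examining the cause of the lack of success", with redesign or stopping named as possibilities and recruitment going on during the evaluation. The upper branch reads "If nine or more success are observed, 30 additional patients will be accrued for a total of 46 patients".

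The article does not give the number of successes needed at 46 patients.

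**The concern.** A Simon design is a set of four numbers: the stage-1 size, the stage-1 futility limit, the total size and the final limit. Its power and alpha belong to that set and not to the sample size alone. The article takes the sizes 16 and 46 from the optimum design and claims that design's 80% power, but prints an interim limit that the design does not have.

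The likely cause is a slip in converting the design's limit (stop at seven or fewer) into words. The correct conversion is fewer than eight / eight or more; the article has fewer than nine / nine or more.

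At stake is the go/no-go decision on the primary endpoint. A trial with exactly 8 successes in 16 (50%, midway between the two benchmarks) would be flagged for possible redesign or stopping, although the named design would carry it on.

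**Working it through.** **Inputs.** From the sample-size paragraphs: p0 = 0.40, p1 = 0.60, power 0.80, total n = 46. From the interim section: n1 = 16, n2 = 30, flag at 8 or fewer, continue at 9 or more. Two assumptions: (a) 95% confidence means one-sided alpha 0.05; (b) the final cut-off is the optimum design's, 24 or more of 46.

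**Formula.** If the trial stops at r1 or fewer successes in stage 1 and succeeds with more than r in total, then

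P(success | p) = sum over x = r1+1 to 16 of b(x; 16, p) × P(Bin(30, p) > r − x).

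**Step 1: reproduce the plan's figure.** The search minimised expected sample size under p0, subject to alpha ≤ 0.05 and power ≥ 0.80. The optimum is r1/n1 = 7/16 and r/n = 23/46: stop at 7 or fewer, continue at 8 or more, succeed at 24 or more. Alpha is 0.0486, power 0.8006, expected n under p0 24.5, and probability of early stopping under p0 0.716. The sizes 16, 30 and 46 and the 80% power all match the article; only the interim limit differs. The match also supports assumption (a): with one-sided alpha 0.025 the optimum is 7/16 and 31/61, which does not give 46 patients and also has a stage-1 limit of 7.

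**Step 2: the printed boundary, enforced as a stopping rule.**

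| Continue at | Succeed at | Alpha (p = 0.40) | Power (p = 0.60) |
|---|---|---|---|
| 8 or more | 24 or more | 0.0486 | 0.8006 |
| 9 or more | 23 or more | 0.0522 | 0.7011 |
| 9 or more | 24 or more | 0.0348 | 0.6838 |
| 9 or more | 25 or more | 0.0213 | 0.6533 |

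The highest power with alpha ≤ 0.05 is 0.684. Under enforcement no final cut-off can give more than P(9 or more of 16 | 0.60) = 0.716, so this conclusion does not depend on assumption (b).

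**Step 3: where the loss arises.** The two rules differ only at exactly 8 of 16. At p = 0.60 this has probability 0.2839 − 0.1423 = 0.142, and such a trial would still reach 24 of 46 with probability P(Bin(30, 0.60) ≥ 16) = 0.825. The product, 0.142 × 0.825 = 0.117, is the loss of power: 0.8006 − 0.6838 = 0.117.

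**Step 4: the flag is never acted on.** The rule then becomes a single-stage test on 46 patients.
- 24 or more: power 0.891, alpha 0.064.
- 25 or more: power 0.825, alpha 0.034.

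**Step 5: false futility flag at p = 0.60.** P(7 or fewer of 16) = 0.142; P(8 or fewer of 16) = 0.284. The ratio is 2.0, and it does not depend on what follows the flag.

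**The case against.** The strongest objection is that the article does not make the boundary binding. Missing it leads to a review of the cause, after which redesign or stopping is optional, and recruitment does not pause. A reader might infer from Step 2 that the trial's power simply is 68%, or that it cannot exceed 71.6%. The text does not support either statement without a condition, because both assume that every trial below nine is terminated. If, for illustration, half of the flagged trials stopped, independently of later results, power at 24 or more of 46 would be (0.684 + 0.891)/2 = 0.787 and alpha (0.035 + 0.064)/2 = 0.049.

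This objection stands as a limit on the size of the effect. It does not reconcile the two sections. The 80% is credited to Simon's optimum design, whose calculation assumes stopping at its limit, and that limit is seven. Always ignoring the flag does not give the stated design either: at the optimum's own final cut-off, alpha is 6.4%, above the 5% implied by 95% confidence.

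Three further points on the other side are fair. The stricter cut-off does not inflate the type I error; if enforced, alpha falls to 3.5%. Only one stage-1 outcome, 8 of 16, is handled differently. And the unstated final cut-off is not itself an error, since a condensed article may leave it to the full protocol or analysis plan.

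Condensation does not explain the nine, however. The number is stated in both branches of the rule, the two branches agree with each other, and nothing elsewhere in the article justifies it.

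**Conclusion.** The inconsistency is real. The interim boundary is one success stricter than the design to which the article attributes its power.

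- **If nine is enforced:** power is 68.4% and alpha 3.5%, assuming success at 24 or more of 46; no final cut-off takes power above 71.6%.
- **As worded, non-binding:** at 24 or more of 46, power lies between 68.4% (flag always stops the trial) and 89.1% (flag never does), and alpha between 3.5% and 6.4%. The article does not fix where in that range the trial falls.
- **In either case:** the chance of a false futility flag at a true 60% rate is 28.4% instead of 14.2%.

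These figures rest on reading 95% confidence as one-sided alpha 0.05, which reproduces the stated sizes exactly. They do not show that the trial as worded has 68% power; that holds only if the boundary is followed as a stopping rule.

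**What to change.** In Interim analysis for futility, change the boundary to fewer than eight / eight or more, pair it with a final criterion of 24 or more successes in 46, and add that the 80% power and 5% alpha hold only if the boundary is followed. Changing the number alone is not enough while the optional wording stays, because overriding the boundary with 24 or more of 46 can bring alpha up to 6.4%.

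If something else is intended, restate the operating characteristics for the rule actually used:

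- **Nine is deliberate and enforced:** about 68% power and 3.5% alpha, with 24 or more of 46.
- **The boundary may be overridden:** use 25 or more of 46. Alpha is then at most 3.4%. Power is 82.5% if the flag never stops the trial, and lower to the extent that it does (65.3% if nine always stops it).

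The cost is a few words in the interim rule and one or two sentences on the final criterion and its condition. No extra patients are needed.

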## Discussion

This multi-centre study aims to accrue 46 patients to test the hypothesis that KIM provides a real-time IGRT solution to improve cancer targeting accuracy, dose delivery and treatment outcomes in patients receiving liver SABR. Several studies have demonstrated liver motion up to several centimetres during treatment [15, 26, 27] and a retrospective review at our institution also demonstrated significant intrafraction motion which would not have been observed without using a real-time imaging system such as KIM.

Other potential benefits of KIM technology include a reduction in imaging radiation dose and overall treatment time compared to current IGRT method of using CBCT. We have demonstrated that continuous kilovoltage imaging results in substantially less imaging dose than multiple CBCT scans. CBCTs are acquired during breath-holds, which is often the reason for long treatment times leading to patient fatigue and instability in the patients’ ability to maintain consistent breath-holds.

The liver is a radiosensitive organ, and particularly in patients with liver cirrhosis, maximum sparing of the functioning liver is a critical goal in SABR. Continuous intrafraction monitoring has the potential to improve the accuracy of treatment delivery for better disease outcome and reduced treatment-related toxicity. Ultimately, if direct intra-fraction visualisation of the target lesion using KIM method is successful, it may help to safely reduce the PTV margins to maximise further liver sparing and minimise toxicity.

## Data Availability

The LARK Trial Management Committee support the use of the data acquired in this study for further research within the bounds of patient privacy and ethics concerns. The protocol states: *De-identified data collected in this study will be stored perpetually and may be used for future research. The stored data will only be used in future research under the approval of a Human Research Ethics Committee*. Researchers interested in the use of the LARK trial data should contact the study authors.

## Abbreviations

CBCT: Cone-Beam Computed Tomography
CTV: Clinical Tumour Volume
DIBH: Deep Inspiration Breath-Hold
EEBH: End-Exhale Breath-Hold
GTV: Gross Tumour Volume
IGRT: Image Guided Radiation Therapy
IMRT: Intensity Modulated Radiotherapy
ITV: Internal Target Volume
KIM: Kilovoltage Intrafraction Monitoring
LARK: Liver Ablative Radiotherapy using Kilovoltage intrafraction monitoring
MLC: Multileaf Collimator
PERCIST: Positron Emission Tomography Response Criteria In Solid Tumours
PTV: Planning Target Volume
QA: Quality Assurance
RECIST: Response Evaluation Criteria In Solid Tumours
RILD: Radiation Induced Liver Disease
SABR: Stereotactic Ablative Body Radiotherapy
SBRT: Stereotactic Body Radiation Therapy
VMAT: Volumetric Modulated Arc Therapy
